### Safety

Adverse events will be monitored by passive self-reporting and active surveillance at each follow-up visit or telephone call; the rates of adverse events within the two treatment arms will be compared. Safety data will be subject to clinical review and summarized by appropriate descriptive statistics. In case of treatment failure the attending physician will prescribe additional antimicrobial treatment, as appropriate. Such 'rescue medication' will be offered by the study team.

An independent Data and Safety Monitoring Board (DSMB) will monitor safety on an ongoing basis throughout the trial. Safety reports summarizing Serious Adverse Events (SAE) will be submitted to the Chair of the DSMB after each SAE. In addition, the DSMB will review the results of the interim analyses scheduled to occur after approximately 25, 50 and 75 percent of the patients have completed until the 10- to 18-days post-treatment visit. The objective of the interim analyses is to consider stopping for safety reasons only. The breaking of the blind and the analysis of the data will be performed by a pharmacist and the members of DSMB. The following stopping rules are predefined during each interim analysis: 1). Regarding the primary outcome measure, Short treatment is definite inferior to Standard treatment with statistical significance of ≥ 95% certainty and 2). The clinical cure rate in the Standard arm is <75%. Besides these stopping rules, the judgment of the DSMB will be based upon a general review of adverse events including 30-day mortality. The initial communication to the study team will consist only of the outcome of the decision: either 1) there is sufficient evidence to consider stopping the trial or 2) there is insufficient evidence to consider stopping the trial.

### Registration

This study is registered at clinicaltrials.gov [NCT00809913] and trialregister.nl [NTR01583] with the acronym FUTIRST-trial used.

## Discussion

UTIs in adults are classified into acute uncomplicated UTI, acute uncomplicated pyelonephritis, complicated UTI (CUTI), acute complicated pyelonephritis and in addition, for men there are several categories of prostatitis [11,12,19,25]. The term 'uncomplicated' is usually restricted to non-pregnant women without underlying functional or anatomical abnormalities of the urinary tract but it remains controversial whether older, postmenopausal, women and women with other underlying co-morbidities, like diabetes mellitus, also belong to this group [20]. Pyelonephritis is defined as a serious infection involving the pelvis, calices and kidney parenchyma which is classically characterized by fever, flank pain or costovertebral angle tenderness and signs and symptoms of UTI. While treatment recommendations of acute uncomplicated UTI and acute uncomplicated pyelonephritis are quite straightforward with short oral antimicrobial courses on an outpatient basis, there is a lack of conformity on therapeutic approaches for CUTI and acute complicated pyelonephritis; likely because these conditions reflect a broad spectrum of clinical syndromes. Therefore from a pragmatic viewpoint it is reasonable to classify these patients according to their clinical presentation in which fever reflects whether there is a parenchymal inflammation or not. Whether this involves the kidney, bladder, prostate, lymph nodes of the pelvis, blood circulation or a combination of those cannot be assessed on clinical grounds. In the literature, fever in UTI is mostly attributed to AP [1,2]. In this study we use febrile UTI as the clinical syndrome of interest because this is how patients present and fever mainly determines the appropriate treatment. According to existing classifications this includes CUTI with fever, (un)complicated AP or, as has been suggested, the urosepsis syndrome [26]. However, for reasons of simplicity and clinical pragmatics we consider FUTI as a clinical appearance of AP [1,2].

This study is different from previous studies that address treatment duration of AP. One study included only women with uncomplicated AP and a median age of 25 years [9] while another recent study included predominantly women aged ≤ 45 years of which a small subgroup suffered complicated AP [10]. Based on the results of these studies, it can be concluded that uncomplicated AP can be effectively treated in young women with a 5–7 day course of fluoroquinolones. However, the treatment duration was not the only study objective because the comparators in these studies were other antimicrobial agents. Therefore it remains unclear whether longer treatment of AP with fluoroquinolones might be even better. Other clinical trials on AP did not examine treatment duration but most of them compared newer or extended release fluoroquinolones to conventional ones. In all these studies, treatment duration was variable being 5 to 14 days [27-31]. From these trials it seems evident that AP in many cases can be treated shorter than 14 days. Nevertheless caution is warranted to generalize this to common practice because the study populations were highly selected being predominantly women who were relatively young and healthy. Furthermore, both patients with AP and CUTI were included in which fever was not a prerequisite of inclusion and the majority of cases had CUTI. In other words one might only conclude from these studies that cystitis in a complicated person can effectively be treated with fluoroquinolones less than 14 days. Based on the evidence in the literature we therefore conclude that the duration of antimicrobial treatment in patients with uncomplicated AP could be as short as 5–7 days whereas in patients with complicated AP it is unclear and should be at least 14 days.

In contrast to previous studies, the current study includes consecutive patients with febrile UTI, being AP, reflecting the daily clinical practice of primary care and emergency departments. This includes male participants who by definition are classified as complicated. This might be controversial but from a pathophysiological point of view there is no reason to believe that AP in men behaves different from AP in women. Indeed, previous studies that included a sufficient number of men, showed that treatment of febrile UTI with fluoroquinolones for 7–14 days had comparable clinical cure rates of about 90% [28,30-32]. Moreover, we recently evaluated the guideline of the Dutch College of General Practitioners that recommends antimicrobial treatment of febrile UTI for 10 days irrespective of sex [33]. In this observational study with similar inclusion criteria, male sex was not a risk factor for clinical failure [21]. As in previous studies, the mortality rate in men was higher but this reflects underlying co-morbidity rather than attributable risk of UTI [5,21]. Based on the results of these studies we conclude there is sufficient evidence to include men in such a trial as this. Furthermore, it should be emphasized that although men with suspected chronic bacterial prostatitis are excluded from this trial it might be that men with febrile UTI have indeed acute prostatitis. However, as recommended treatment durations of acute prostatitis are primarily based on expert opinion (being 14 days) and the distinction of febrile UTI in men between pyelonephritis or prostatitis can often not be made clinically, a trial evaluating the optimal treatment duration is even more relevant in this population [34].

In contrast to all previous studies, the study objective of this trial only involves treatment duration. Combined with the inclusion of patients reflecting routine daily practice these aspects are thus unique that it is named with the acronym FUTIRST (Febrile UTI Randomized Short Treatment)-trial to put emphasis on being the first clinical trial on febrile UTI or AP with such a pragmatic design. Meeting the criteria for a practical clinical trial, the results of this study are thus generalizable to other settings and should influence policy makers of treatment guidelines on AP [35].

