**Discussion:**

This study aims to demonstrate that 7 days of antimicrobial treatment is non-inferior as compared with 14 days of treatment in patients with febrile urinary tract infection. In addition, it will generate insights into the side-effects of antimicrobial treatment in relation to its duration. The study population will also include men, the elderly and patients with significant co-morbidity. Reflecting daily practice of primary health care and emergency departments, the results of this study can be generalized to other locations.

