## Background

Fever in urinary tract infection (UTI) suggests the presence of tissue inflammation and is therefore considered to be a sign of acute pyelonephritis (AP) [1,2]. In 2000, the estimated direct and indirect costs of acute AP in the United States were $2.14 billion which is predominantly related to hospitalization [3]. In the last decades hospitalization rates of patients with AP has decreased from almost 100% to 10–30% [4-6]. The outpatient management of patients with AP has become popular as have oral antimicrobial treatment regiments and shortening of treatment duration [7-10]. However, such approaches have only been studied in the setting of uncomplicated AP, defined as AP in a young otherwise healthy non-pregnant woman without co-morbidity. In contrast to this, the optimal treatment of patients with complicated AP remains unclear and, not surprisingly, treatment guidelines therefore almost exclusively discuss uncomplicated AP [11,12]. Current strategies recommend antimicrobial treatment for at least 14 days [13-16].

Facing the aging of the general population it is challenging to better define the optimal treatment for AP in an unselected population including the elderly, men and patients with co-morbidity. Moreover, fluoroquinolones, being the preferred oral empirical treatment for AP, are associated with considerable side effects such as dysglycemia and *Clostridium difficile *infections, especially in the elderly and subjects with co-morbidity [17,18]. Therefore it is questionable whether the benefit of antimicrobial treatment of AP at the end of a 14-day antimicrobial treatment still outweighs its potential side effects.

We will conduct a multicenter, randomized, double-blind, non-inferiority trial to determine whether the efficacy and safety of a 7-day antimicrobial regimen is similar to a 14-day antimicrobial regimen in unselected individuals presenting with AP, defined as febrile UTI, at primary care or emergency department.

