#### Definitions

The following definitions will be used. *Clinical cure *is defined as being alive with the absence of fever (temperature < 38.0°C) and the resolution of UTI symptoms (either absence of symptoms or at least 2 points improvement on a 0 through 5 points severity score) through the post-treatment visit whereas no additional antimicrobial therapy for a relapse of UTI is described. *Clinical treatment failure *is the opposite of clinical cure and defined as deterioration, persistent fever and/or symptoms of UTI (less than 2 points improvement on a 0 through 5 points severity score) or relapse of UTI with the same uropathogen for which additional antimicrobial treatment is prescribed. *Clinical recurrence *is defined as any clinical UTI after clinical recovery and the end of treatment period including uncomplicated UTI, complicated UTI and acute pyelonephritis as defined previously [19]. Based on microbiological typing of isolated uropathogen distinction will be made between clinical relapse, being the same uropathogen or clinical reinfection with a different uropathogen. *Pre-treatment significant growth of uropathogens *is defined as ≥ 10^4 ^colony forming units/mL in women (midstream urine) or ≥ 10^3 ^colony-forming units/mL in men (midstream urine) or ≥ 10^3 ^colony-forming units/mL (catheter urine) or ≥ 10^2 ^colony-forming units/mL of midstream urine collected during antibiotic treatment of UTI at study entry [19]. *Bacteriologic cure *or eradication is defined as the elimination of the study entry uropathogen or as pathogen growth of less than 10^4 ^colony forming units/mL in women or less than 10^3 ^colony-forming units/mL in men, of a midstream urine sample collected combined with the disappearance of leucocyturia [19]. *Bacteriologic failure *through the 10- to 18-day post-treatment visit is defined as the absence of bacteriologic cure and classified as persistence of the original pathogen or superinfection with a new pathogen on the basis of species determination and antibiogram or an alternative method, such as Amplified Fragment Length Polymorphism or sequence-based PCR using repetitive extragenic palindromic primers. *Ciprofloxacin resistance *of uropathogens is defined by a MIC > 4 mg/L and includes all *Enterococcus spp. Acute complicated pyelonephritis *is defined as febrile urinary tract infection in a person with one or more of the following baseline characteristics: male sex, postmenopausal (female aged ≥ 50 years), underlying urinary tract disorder (e.g. nephrolithiasis, urologic malignancy, vesicoureteral reflux, urethral stricture), diabetes mellitus, immunocompromised, renal insufficiency or progressive UTI despite antimicrobial UTI treatment. *Co-morbidity *is defined as the presence of any urinary tract disorder, heart failure, cerebrovascular disease, renal insufficiency, diabetes mellitus, malignancy or chronic obstructive pulmonary disease for which the patient is prescribed medication and/or consults a hospital-based medical specialist.

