#### Intention to treat, per-protocol and subgroup analysis

The primary endpoint will be analyzed on the Intent-To-Treat population, including all randomized patients who received at least one dose of the study drug, and on the Per-Protocol population, including all randomized patients who had been given the study drug for a minimum of 24 hours (in case of treatment failure) or who had been taken at least 80% of the study drug (in case of clinical cure). The primary significance test will be carried out on the equivalence in cure rates or clinical failure rates in the two treatment arms.

Descriptive statistics will be used to describe the baseline characteristics of the participants in each arm. Binomial or categorical outcome measures will be analyzed using Chi-square tests (Pearson's or Fisher's). Risk difference with 95% CI will be used to compare the differences of categorical outcomes. The primary outcome variable is clinical cure rate assessed 10- to 18 days post-treatment. As we are only interested in non-inferiority and not in equivalence, the sample size calculation is based on a one-tailed alpha of 0.05. This implies that the 90% CI of a two-tailed Chi-square test should not cross the predefined risk difference of 10% lower clinical cure rate [24].

The primary outcome will additionally been tested in the subgroups of males, females, patients with acute complicated pyelonephritis, patients with any co-morbidity, patients aged ≥ 50 years, patients with bacteremic UTI and patients with stepdown treatment (antimicrobials intravenously followed by oral ciprofloxacin during the first 7 days). Subgroup analysis and all secondary outcome measures will be analyzed using Chi-square tests.

In case of significant differences in baseline characteristics, which may have happen by chance as we only stratify randomization by sex and center, the primary outcome will additionally be tested using a multivariable binary logistic regression model to adjust for the following potential confounders: age, acute complicated pyelonephritis, underlying co-morbidity and the use of stepdown treatment.

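### Complicated pyelonephritis is named as the open question, but its planned subgroup analysis has no non-inferiority margin and no stated bearing on the conclusion

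*Protocol article*

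**What the plan says.** **The gap in knowledge.** The Background says that "the optimal treatment of patients with complicated AP remains unclear". The Discussion concludes, of treatment duration, that it "in patients with uncomplicated AP could be as short as 5–7 days whereas in patients with complicated AP it is unclear".

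**The objective and the patients.** The Background sets the aim as finding out whether the "efficacy and safety of a 7-day antimicrobial regimen is similar to a 14-day antimicrobial regimen in unselected individuals presenting with AP". Enrolment is consecutive. On the syndrome studied, the Discussion says: "According to existing classifications this includes CUTI with fever, (un)complicated AP". Under Definitions, a patient counts as complicated with any one of a list of features that begins "male sex, postmenopausal (female aged ≥ 50 years), underlying urinary tract disorder" and goes on to diabetes, immunocompromise, renal insufficiency and progression despite treatment. Randomization is stratified by center and sex, not by complicated status.

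**The decision rule.** Sample size sets a 10-point margin, one-sided alpha 0.05 and 200 evaluable patients per arm. The analysis section applies a 90% CI to the pooled Intent-To-Treat and Per-Protocol populations. It then adds: "The primary outcome will additionally been tested in the subgroups of males, females, patients with acute complicated pyelonephritis", followed by further subgroups. All subgroup analyses use chi-square tests. No margin is given for any subgroup, and nothing says how a subgroup result affects the conclusion.

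**The intended use.** The abstract stresses that "The study population will also include men, the elderly and patients with significant co-morbidity". The main Discussion says that the results "should influence policy makers of treatment guidelines on AP", with no limit by type of patient.

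**The concern.** The protocol singles out complicated pyelonephritis as the group in which shorter treatment is unproven. Its only non-inferiority test is run in a mixture of that group and uncomplicated patients. If the true difference is smaller in uncomplicated patients, they pull the pooled difference toward zero, and in a non-inferiority trial that is the direction of success. The pool could then pass while complicated patients sit at the margin.

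The planned subgroup analysis does not guard against this. A chi-square test asks whether the arms differ, and a non-significant result in a subgroup does not show non-inferiority. At stake is whether a positive trial supports a statement about complicated patients in particular, who are the reason given for running it.

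**Working it through.** **Inputs from the Sample size section:** cure 90% (Standard) and 89.5% (Short), margin 10 points, one-sided alpha 0.05, power 90%, 200 evaluable per arm.

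**Assumptions, not in the article:** 90% cure on standard treatment in both types of patient; no deficit in uncomplicated patients; a true deficit D = 10 points in complicated patients; complicated share s of 90%, 80% or 70%.

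**1. The plan's own figure.** The unpooled formula gives n = (1.645 + 1.282)² × (0.90×0.10 + 0.895×0.105) / (0.10 − 0.005)² ≈ 175 per arm. With a continuity correction, (175/4) × [1 + √(1 + 4/(175×0.095))]² ≈ 196, which is close to 200. Power at 200 is about 93% without the correction and 91% with it. The planned size is therefore sound for the pooled test.

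**2. Dilution.** Pooled deficit = s × D. The pool passes when p_Short − p_Standard − z × √[p_Short(1 − p_Short)/200 + p_Standard(1 − p_Standard)/200] > −0.10. The value z = 1.645 is the 90% CI rule of the analysis section; z = 1.96 is the 95% CI that the Sample size section mentions, so both are shown. Exact binomial enumeration gives:

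| Complicated share | Pooled deficit | Pass, 90% CI | Pass, 95% CI |
|---|---|---|---|
| 100% | 10 points | 5% | 3% |
| 90% | 9 points | 9% | 5% |
| 80% | 8 points | 15% | 9% |
| 70% | 7 points | 23% | 15% |

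Hand check at 80%: Short cure 0.82; SE = √[(0.09 + 0.82×0.18)/200] = 0.0345; Φ(0.02/0.0345 − 1.645) = Φ(−1.065) ≈ 14%, in line with the exact 15%.

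**3. What the planned chi-square test can show.** With 140, 160 or 180 complicated patients per arm (70%, 80% or 90% of 200), a two-sided 5% test of 90% v 80% has about 65%, 71% or 76% power to detect a true 10-point deficit. It would therefore miss such a deficit between a quarter and a third of the time.

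**4. What a margin-based test there would cost in power.** With true rates of 90% and 89.5%, power = Φ(0.095/SE − z), where SE = √[(0.09 + 0.895×0.105)/n]. At n = 140, SE = 0.0363, giving about 84% (z = 1.645) or 75% (z = 1.96). At n = 180, SE = 0.0320, giving about 91% or 84%. In 80 men per arm (40% of 200, again assumed), exact power is about 64% (z = 1.645).

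**The case against.** **Pooling matches the objective.** The aim is stated for unselected patients with febrile UTI, and the Discussion explains why the clinical syndrome was preferred to finer classes. This stands. The pooled test is the right primary test, and the point concerns only what is said about complicated patients after it passes.

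**Error rate.** A reader might set the 9–23% against the nominal 5% and infer an inflated type I error. That does not follow. The nominal level belongs to the pooled null hypothesis, and when the pooled deficit is 10 points the test keeps its size (first row of the table).

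**Uncomplicated patients.** A reader might also infer that the protocol treats 5–7 days as settled in them, so that they contribute nothing. The Discussion does not go that far. It notes that the earlier trials compared different drugs as well as durations, and that a longer fluoroquinolone course might still do better. The zero deficit used above is therefore an assumption of this review.

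**Men.** If 40% of patients were men and only men lost 10 points, the pool would pass 59% of the time (46% with the 95% CI). This does not illustrate the point: most of that dilution could come from women who are themselves complicated by definition, and the Discussion argues that men should not respond differently.

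**Likely size.** Because all men and all women aged 50 or over count as complicated, the uncomplicated share may be small and the effect near the 9% end.

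**Already partly planned.** The subgroup is pre-specified, and risk differences with 95% CIs are planned for categorical outcomes in general. That helps. Still, the article itself fixes chi-square as the subgroup method, and neither provision attaches a margin or a consequence to the result.

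**Conclusion.** The point holds as a limited one. The pooled test is valid for the stated objective and should stay. The weakness is that the group named as the open question gets a difference test without a margin, and its result has no stated role in the conclusion. If uncomplicated patients have no deficit and complicated patients have one of exactly 10 points, the pool passes about 9%, 15% and 23% of the time with 90%, 80% and 70% complicated (90% CI rule), or 5%, 9% and 15% (95% CI rule). These figures assume 200 evaluable per arm and 90% cure on standard treatment. The article gives neither the shares nor the deficit by type of patient, so they show a range and do not predict. The effect shrinks if uncomplicated patients are few or share the deficit. The documents do not support a claim that the primary analysis is biased or that the pooled population is wrong. The change is a worthwhile, inexpensive improvement.

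**What to change.** In the analysis section:

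- Keep enrolment, randomization and the pooled primary test as they are.
- After pooled non-inferiority is shown, test the risk difference and its CI in acute complicated pyelonephritis against the same 10-point margin, as a fixed-sequence key secondary. This replaces the chi-square test in that subgroup.
- State that non-inferiority is claimed specifically for complicated pyelonephritis only if that interval excludes a 10-point deficit. Otherwise the conclusion refers to the pooled population only.
- Report the risk difference and CI for men and for women beside the margin, descriptively and without a formal condition. A condition in men would often fail by chance: at about 64% power with 80 per arm, nearly equal treatments would miss it about 36% of the time.

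**Cost.** Wording only. There are no extra patients, and the fixed order takes no alpha from the pooled test. The downside is lower power for the specific claim: about 84–91% with 140–180 complicated patients per arm under the 90% CI rule. Those figures are for the subgroup step alone, so the chance of passing both steps is somewhat lower. The interval in men will be wide.
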